**Methods:**

This prospective, multicenter, randomized controlled, single-blinded, phase III trial is designed to enroll 512 eligible patients with advanced rectal cancer and preoperative enlarged lateral lymph nodes. The population will be randomly assigned into the solely total mesorectal excision (TME) group or the TME + LLND group after eligible selection. The primary outcomes are to be 3-year local recurrence rate and 3-year disease-free survival, and the secondary outcomes include 3-year overall survival, 1-year sexual and urinary function, and perioperative outcomes.

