### Outcomes

The primary outcomes of this trial are the 3-year local recurrence rate and 3-year disease-free survival (DFS). The local recurrence is defined as recurrent disease in the pelvis or at the incision and DFS is defined as the time of surgery to the recurrence or end of follow-up. It is diagnosed using the following methods: (1) histological confirmation by biopsy, (2) confirmation by positron emission tomography-computed tomography (PET-CT), (3) CT/magnetic resonance imaging (MRI) shows that there is a mass in the pelvis which is growing with/without symptoms.

The secondary outcomes include 3-year overall survival (OS) and disease-free survival (DFS) at 3 years post surgery, sexual and urinary function at 1 year post surgery, and perioperative outcomes. OS is defined as the time of surgery to the date of death from any cause or the date of follow-up. Sexual function for men and women is assessed by using the International Index of Erectile Function-5 scoring system (IIEF-5) and the Female Sexual Function Index (FSFI), respectively [20, 21]. Urinary function is assessed by using the International Prostate Symptom Score (IPSS) [22]. Perioperative outcomes include operation time, intraoperative blood loss, intraoperative transfusion, incision length, intraoperative complications, time to first flatus, time to liquid diet intake, postoperative hospitalization days, postoperative complications, and mortality.

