### Follow-up

All participants will be followed up regularly as per schedule (Table 2). Biopsy or PET-CT would be done when it is necessary to diagnose recurrence.

**Table 2 Tab2:** Trial schedule

Measures	M1	M3	M6	M9	M12	M18	M24	M30	M36
Physical examination	×	×	×	×	×	×	×	×	×
Blood test	×	×	×	×	×	×	×	×	×
CEA	×	×	×	×	×	×	×	×	×
CA 19-9	×	×	×	×	×	×	×	×	×
CT of chest			×		×	×	×	×	×
CT/MRI of abdomen and pelvis			×		×	×	×	×	×
Colonoscopy			×		×	×	×	×	×
IIEF-5	×	×	×	×	×				
FSFI	×	×	×	×	×				
IPSS	×	×	×	×	×				

*CA* cancer antigen, *CEA* carcinoembryonic antigen, *CT* computed tomography, *FSFI* Female Sexual Function Index, *IIEF* International Index of Erectile Function, *IPSS* International Prostate Symptom Score, *M* month*, MRI* magnetic resonance imaging

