### Sample size and statistical analysis

Our trial aims to demonstrate that LLND could decrease the 3-year local recurrence rate of low rectal cancer patients with suspicion of LLN metastases. Based on previous studies, we assume that the 3-year local recurrence rate for patients with suspicion of LLN metastases who do not undergo LLND is 15% [13–16], and LLND is expected to show a reduction of 7 percentage points. G*Power 3.1 is used to calculate the sample size. A statistical power of 0.80 and a significance level of 0.05 are chosen, and we assume that there will be a 10% dropout rate. Therefore, 512 patients are needed in this specific trial (256 patients in each group).

All participants in this trial will be analyzed using the intention-to-treat analysis. The chi-square test and Student’ *t* test will be used to compare categorical data and continuous data for the two groups, respectively. The 3-year local recurrence rate, the primary endpoint of this trial, will be analyzed using the Kaplan-Meier method, as well as OS and DFS. In addition, based on different characteristics (such as age, sex, tumor stages, etc.), which can identify the influence of competing risk factors, the Cox proportional hazards (PH) regression model will be tested if Schoenfeld Residuals Analysis confirms PH assumption validation. Otherwise, an alternative extended Cox PH model will be used. SPSS 21.0 (SPSS Inc., Chicago, IL, USA) will be used for all statistical analyses, and a *P* value < 0.05 is considered significant.

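### Functional scores are collected at five visits, but the only stated test for continuous data, applied to the named 1-year outcome, uses just the last one; a repeated-measures model would use them all (minor)

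*Protocol article*

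**What the plan says.** The Outcomes section lists, among the secondary outcomes, "sexual and urinary function at 1 year post surgery, and perioperative outcomes". The Abstract agrees: "the secondary outcomes include 3-year overall survival, 1-year sexual and urinary function, and perioperative outcomes". Sexual function is scored with IIEF-5 in men and FSFI in women, and urinary function with IPSS.

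Table 2, in the Follow-up section, marks all three instruments at M1, M3, M6, M9 and M12.

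The section on sample size and statistical analysis gives one general sentence on methods for data that are not time-to-event: "The chi-square test and Student’ *t* test will be used to compare categorical data and continuous data for the two groups, respectively". It names no instrument and no visit. The same section states: "All participants in this trial will be analyzed using the intention-to-treat analysis". It gives no rule for missing scores.

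**The concern.** Each patient is due five functional assessments, and one of them is a named outcome. A two-group t test on that outcome leaves the other four (4/5 = 80%) out of any named comparison. It also cannot use a patient who gave scores up to month 9 but not at month 12, unless a value is filled in. That sits awkwardly with the promise to analyse every participant by intention to treat.

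Two features make this worth raising. The Background gives worse quality of life as one of the main arguments against LLND, and these three questionnaires are the only patient-reported measures in the document. The Dropping out section also allows exit because of adverse events, by the investigator in the patient's interest, by refusal, or for poor compliance. Some of these could follow from poor function, so absence at month 12 may depend on the score being measured. At stake are some attenuation and loss of precision in the 1-year comparison, and the lack of a defined early comparison.

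**Working it through.** **No plan figure to reproduce.** The document gives no standard deviation, effect size, sex split or month-12 missingness for any functional score. The inputs taken from it are 256 patients per arm, 10% dropout (assumed there for the 3-year local recurrence sample size) and five visits. Everything else below is an assumption.

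**1. What each method uses**

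| | M1–M9 scores | Patient with no M12 score |
|---|---|---|
| t test at M12 | not used | contributes nothing unless imputed |
| Repeated-measures model, M1–M12 | used | contributes through earlier scores |

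**2. Bias when dropout depends on function.** The simulation had 1,500 trials per scenario, 256 per arm, a true difference of 0.40 SD at every visit, and equal correlation ρ between visits. M12 missingness was logistic in the M9 score, with the same rule in both arms. The mean t-test difference at M12, with the shortfall (0.40 − estimate)/0.40, was:

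| Missing at M12 | ρ | log-odds slope 1.0 per SD | log-odds slope 1.5 per SD |
|---|---|---|---|
| 10% | 0.5 | 0.386 (3.5%) | 0.375 (6.3%) |
| 10% | 0.7 | 0.377 (5.8%) | 0.368 (8.0%) |
| 30% | 0.5 | 0.372 (7.0%) | 0.357 (10.8%) |
| 30% | 0.7 | 0.359 (10.3%) | 0.336 (16.0%) |

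A likelihood-type estimate using M1–M9 (regress M12 on the earlier scores with arm intercepts, then average over all patients) gave 0.397–0.406 throughout. An independent rerun gave 0.370–0.387 for the t test at 10% missing, 0.335–0.371 at 30%, and 0.398–0.404 for the estimate using earlier scores.

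**3. Bias against sampling error.** At 10% loss there are about 230 patients per arm, so the standard error of the difference is √(2/230) = 0.093 SD. The bias is 0.40 − 0.386 = 0.014 to 0.40 − 0.368 = 0.032 SD. That is 0.014/0.093 = 0.15 to 0.032/0.093 = 0.34 of one standard error.

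**4. Precision when dropout is unrelated to function.** Neither method is then biased. With four earlier visits and equal correlation, R² = 4ρ²/(1 + 3ρ). With a fraction m missing at M12, the variance of the model estimate relative to M12 completers is 1 − mR². The effective n per arm is 256(1 − m)/(1 − mR²).

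| ρ | R² | m = 10%: ratio, n (completers 230) | m = 30%: ratio, n (completers 179) |
|---|---|---|---|
| 0.4 | 0.291 | 0.971, 237 | 0.913, 196 |
| 0.6 | 0.514 | 0.949, 243 | 0.846, 212 |
| 0.8 | 0.753 | 0.925, 249 | 0.774, 231 |

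In the simulation the standard-error ratio was 0.98 at 10% missing, and 0.89 at 30% with ρ = 0.7. The formula gives √0.81 = 0.90 for the latter.

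The difference detectable with 80% power (two-sided 5%) is 2.80 × √(2/n). It is 0.248 SD with no loss and 0.261 SD with 10% lost. With the model at 10% loss it is 2.80 × √(2/237) = 0.257 to 2.80 × √(2/249) = 0.251 SD.

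**5. Scope.** The 256 per arm applies to IPSS only. IIEF-5 and FSFI each apply to one sex, so their numbers are smaller and their standard errors larger. The document gives no sex split.

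**The case against.** A reader might go further and infer three things that the document does not support.

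- **That early harm from LLND will not be reported.** No sentence bars reporting the month 1 to 9 scores. Postoperative complications and mortality are secondary outcomes, and all adverse events must be recorded and reported.
- **That patients without a month-12 score are excluded by rule.** The article promises intention to treat and is silent on missing scores. Silence is not a complete-case rule.
- **That LLND will be made to look safer than it is.** That needs a real harm, and dropout that tracks function. Neither is established.

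The t-test sentence is also generic, so the test could be run at each visit. Naming 1 year as the outcome while collecting interim scores is a legitimate choice and no contradiction. The covariance structure and missing-data rules for a secondary outcome are commonly left to a full protocol or SAP, neither of which is shown.

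The numbers can be challenged too. The slopes are strong (odds ratios of about 2.7 to 4.5 per SD), and nothing in the document points to 30% missing at month 12. The simulation leaves only month 12 incomplete and lets missingness depend only on an observed score, so a likelihood method recovers the truth by construction. At 10% loss the 0.40 SD difference would still be seen, at about four standard errors (0.37/0.093).

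All of this stands as a limit on severity. It does not remove the point: a method for continuous data is stated, and for this outcome a better one is available on data already being collected.

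**Conclusion.** The point holds as a minor improvement in the choice of analysis. As written, the named outcome and the stated test together use one of five scheduled scores per patient. The earlier scores have no named comparison.

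Under the assumed correlations (0.5–0.7), dropout slopes (1.0–1.5 log-odds per SD) and true difference (0.40 SD), the 1-year difference is understated by about 3–8% at 10% loss. That is at most about a third of one standard error. The figure of up to about 16% depends on a 30% loss that the document does not suggest. With dropout unrelated to function, the bias is nil and the gain in precision is modest: 3% to 7.5% lower variance at 10% loss for ρ between 0.4 and 0.8. The firmer benefit is a defined set of early contrasts. The sizes that depend on 256 per arm apply to IPSS alone.

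**What to change.** In the section on sample size and statistical analysis, state that IIEF-5 (men), FSFI (women) and IPSS are each analysed with a mixed model for repeated measures on all scores from M1 to M12, with arm, visit, arm-by-visit interaction and an unstructured covariance. Then:

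- keep the M12 arm contrast as the 1-year outcome;
- report the M1, M3, M6 and M9 contrasts with 95% confidence intervals as descriptive safety results;
- keep the M12 t test as a sensitivity analysis;
- report deaths before M12 by arm alongside the model.

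The cost is wording only. No visits, data or staff are added, and the planned SPSS software can fit the model. There are two downsides. The model relies on data being missing at random, and it implicitly estimates function after death as though those patients had lived, which is why the deaths need to be shown beside it.

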### Intervention

After randomization, all participants will firstly receive a cycle of 5-fluorouracil with oxaliplatin therapy (FOLFOX) or capecitabine (Xeloda) with oxaliplatin therapy (XELOX). Subsequently, radiotherapy with 50.4 Gy is administered in 28 separate doses. Next, three cycles of FOLFOX or XELOX will be continued. About 3 to 4 weeks later, patients allocated to the TME group will undergo standard TME surgery solely, while patients allocated to the TME + LLND group will undergo standard TME surgery plus LLND. The extent of LLND includes bilateral LLND (lymph node groups 263P, 263D, and 283). If the short-axis diameter of the external iliac or common iliac lymph nodes is beyond 6 mm, lymph node groups 293, 273, and 280 will be dissected. Unilateral LLND will be done only when the center of the rectal tumor is limited to a single side (not beyond the midline) and the contralateral lymph nodes are not enlarged. Adjuvant chemotherapy, consistent with the preoperative scheme in every patient, will be continued until reaching eight cycles.

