## Discussion

Currently, the hot issue of the treatment of LLN in advanced rectal cancer patients is still being debated in different regions. Eastern countries, especially Japan, favor LLND following TME; however, Western countries believe that nCRT and TME is recommended, and LLDN is added only when a LLN is preoperatively diagnosed as metastatic. Actually, preoperatively enlarged LLNs are not common and only a small proportion of LLDs with a maximum short-axis diameter ≥10 mm, or with a spiculated or indistinct border, or a mottled heterogenic pattern are diagnosed as metastatic [23]. The remaining large proportion of LLNs are underdiagnosed as being metastatic and often confuse surgeons’ treatment strategy. Thus, our trial pays particular attention to this stratification of suspicious LLNs, assessing the efficacy and safety of the LLND in advanced rectal cancer patients.

Another issue we have considered in our trial is the randomization time. In our trial, we randomly allocated participants before nCRT rather than after nCRT. Because LLN metastases are commonly diagnosed before nCRT by their features on pelvic MRI or CT and when chemo-radiation has achieved its effect, the treatment-sensitive regions of any enlarged LLNs will have decreased in size which may confuse the randomization if allocation is performed after nCRT.

This trial is the first randomized controlled trial to investigate the role of LLND in reducing local recurrence rates for low advanced rectal cancer patients with suspicion of LLN metastases. If the efficacy of LLND is verified, which reduces the local recurrence rate from 15% to 8%, LLND can be recommended as a new standard strategy for low advanced rectal cancer patients with suspicion of LLN metastases.

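### DFS and OS start at surgery, but randomisation precedes months of neoadjuvant treatment, so the promised intention-to-treat analysis of all participants cannot be done with these definitions

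*Protocol article*

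**What the plan says.** All references are to the protocol article.

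- **Endpoints (Outcomes).** For overall survival: "OS is defined as the time of surgery to the date of death from any cause or the date of follow-up". For disease-free survival, named there as a primary outcome: "DFS is defined as the time of surgery to the recurrence or end of follow-up". DFS appears again in the list of secondary outcomes, with the landmark "disease-free survival (DFS) at 3 years post surgery". No time origin is given for local recurrence, the other primary outcome.
- **Time of randomisation (Discussion).** "we randomly allocated participants before nCRT rather than after nCRT".
- **What follows randomisation (Intervention).** "After randomization, all participants will firstly receive a cycle of 5-fluorouracil with oxaliplatin therapy (FOLFOX" or the XELOX alternative); then "radiotherapy with 50.4 Gy is administered in 28 separate doses"; then "three cycles of FOLFOX or XELOX will be continued"; then an interval of about 3 to 4 weeks before surgery.
- **Population (Sample size and statistical analysis).** "All participants in this trial will be analyzed using the intention-to-treat analysis". Local recurrence, OS and DFS are to be analysed by Kaplan-Meier.
- **Eligibility (Table 1).** Some criteria can be judged only after randomisation: that mesorectal excision was done, that the resection was R0, and that nodes did not grow by more than 30% after neoadjuvant treatment.

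**The concern.** An intention-to-treat time-to-event analysis needs a start time that every randomised patient has. Surgery is a post-randomisation event that some patients may never reach. The section on dropping out allows withdrawal for refusal, unacceptable adverse events, investigator decision, unapproved other treatment, pregnancy or poor compliance, and each of these can occur during neoadjuvant treatment. Under the written definitions such patients cannot be placed on a DFS or OS curve.

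The first thing at stake is what the results describe: 3-year DFS and OS in patients who completed neoadjuvant treatment and were operated on, not in those randomised. The second is comparability. Randomization and blinding allows participants, surgeons and investigators to know the assignment. Who reaches surgery, and when, could therefore depend on whether the larger operation is planned.

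**Working it through.** **1. Can the definitions and the population both hold?**

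| Randomised patient | Time zero for DFS and OS as written | Consequence |
|---|---|---|
| Operated, R0 | Date of surgery | Included |
| Operated, not R0 | Date of surgery | Fails a Table 1 criterion; DFS counts only recurrence, so status is undefined |
| Withdraws or progresses, never operated | None | Cannot enter either curve |
| Dies before surgery | None | Not an OS event, although OS counts death from any cause |

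The last two rows contradict an analysis of all participants. The order of events alone shows this, whatever the length of the gap.

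**2. Length of the gap.** The numbers of cycles and fractions and the final wait come from Intervention. Cycle length (2 or 3 weeks) and five fractions a week are assumptions, since the article states neither.

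Gap = (1 + 3) × cycle length + 28/5 + wait

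- Shortest: 4 × 2 + 5.6 + 3 = 16.6 weeks; 16.6 × 7 / 30.44 = 3.8 months.
- Longest: 4 × 3 + 5.6 + 4 = 21.6 weeks; 21.6 × 7 / 30.44 = 5.0 months.

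Delays would add to this.

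**3. How many patients could be affected.** The article gives no rate of not reaching surgery. On the planned 512:

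| Assumed share not operated | Patients without a time zero |
|---|---|
| 2% | 0.02 × 512 ≈ 10 |
| 5% | 0.05 × 512 ≈ 26 |
| 10% | 0.10 × 512 ≈ 51 |

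**4. Does moving the origin suffice?** For OS, yes: everyone has a randomisation date, and death from any cause is already the event. For DFS, no. The written definition has recurrence as its only event. At randomisation the tumour is still in place, so a patient never resected, or resected without R0, has persistence or progression and not recurrence. That patient would gain a start time but no defined event. Local recurrence has the same gap. The post-randomisation items in Table 1 would also still exclude these patients.

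**5. Effect on the 3-year landmark.** Thirty-six months from randomisation is 36 − 5.0 = 31.0 to 36 − 3.8 = 32.2 months after surgery. Table 2 does not state its origin. If it runs from surgery, the M30 scan falls at 33.8 to 35.0 months from randomisation and the M36 scan at 39.8 to 41.0 months. M30 would be the last scheduled scan before the landmark.

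**The case against.** **An analysis plan could settle this.** Handling of patients without an operation is often left to that document, and it is not shown here. But the article does more than stay silent: it fixes surgery as time zero and promises intention to treat. An analysis plan would have to override one of the two.

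**The surgery origin fits Table 1.** The operative criteria suggest that the intended population is operated, R0 patients, and for them a surgery origin is coherent. This is a fair reading, but it moves the conflict to eligibility, because those criteria are known only after randomisation. It shows that re-timing the endpoints is not enough.

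**The dropout allowance covers it.** The sample size assumes 10% dropout, which may include losses before surgery. That concerns numbers; it gives these patients neither a start time nor a place in the analysis.

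**Bias is not shown.** A reader might infer that the comparison is already biased or that randomisation has lost its force. The documents do not support that. Planned pre-operative treatment is the same in both arms, and patients are told treatment details on admission the day before surgery, which, if it is when they learn their arm, would limit arm-driven refusal during neoadjuvant treatment. Against this, the same section allows all parties to know the assignment, and refusal at that late point would still come before time zero. Differential loss is therefore possible, not established.

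**Conclusion.** The inconsistency stands. With DFS and OS starting at surgery and randomisation before neoadjuvant treatment, the stated intention-to-treat analysis of all participants cannot be done for a primary outcome or for OS. This rests only on the order of events. The gap of 3.8 to 5.0 months rests on the assumed cycle lengths and fractions per week. The 10, 26 or 51 patients are illustrations, not estimates. The loss may differ by arm and so may weaken the protection of randomisation; its size and direction cannot be derived from the article.

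Two further inferences should be resisted. Local recurrence should not be said to run from surgery, because its origin is not stated. Nor does changing the origin alone cure the problem: it repairs OS, but DFS and local recurrence also need event rules for unresected and non-R0 patients.

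**What to change.** 1. Time OS, DFS and local recurrence from the date of randomisation for everyone randomised.
2. Give DFS status (event and date) for death from any cause, for progression that prevents resection, and for no resection or a non-R0 resection. State how such patients count for local recurrence.
3. State that the Table 1 criteria known only after randomisation do not remove patients from the intention-to-treat set.
4. Keep the surgery-origin analysis in operated patients as supportive. Keep perioperative and functional outcomes timed from surgery.

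**Cost.** The change needs revised endpoint definitions and a reconciled eligibility statement, so it reaches beyond the analysis plan. Recurrence and vital status must be collected for patients not operated on. Early events, before the arms differ in treatment, dilute the contrast slightly. If Table 2 runs from surgery, a landmark at 36 months from randomisation leaves out what the M36 scan first detects; comparing whole curves with all follow-up to M36 avoids discarding those events.
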